# STATISTICAL CONSIDERATIONS

## Number of subjects to include

To investigate the effect of exposure to a music intervention session during botulinum toxin injections on injection-induced stress at injection visit #1, 35 patients per group are required to detect an absolute difference in HRV variation, specifically for the LF/HF ratio, of at least 1.8 with a standard deviation of 2.3, assuming a two-sided type I error rate of 5% and a statistical power of 90%.

The assumptions regarding the expected difference and standard deviation were based on a previous study conducted by our team (Clinical Trials NCT05364203).

More specifically, a difference of 1.8 with a standard deviation of 2.3 for the LF/HF ratio corresponds to an effect size of approximately 0.8, which can be considered large and clinically relevant according to Cohen’s guidelines. Our institution has conducted several studies where this outcome measure was used; effect sizes between 0.5 and 1 have generally been observed, corresponding to differences of 1 to 2 points in the LF/HF ratio. In the Clinical Trials NCT05364203 study investigating the effect of virtual reality, a difference of 1.8 points was demonstrated.

Ultimately, it is proposed to include 40 patients per group to account for potentially unusable data for the primary outcome measure and to ensure sufficient statistical power

## Data analysis: general aspects

The statistical analyses will be conducted using Stata software (version 15, StataCorp, Texas, USA).

Continuous variables will be presented as mean and standard deviation or median and interquartile range, depending on their statistical distribution. The normality of continuous variables will be assessed using the Shapiro-Wilk test and the density curve. Categorical variables will be expressed as counts and percentages. Graphical representations will be provided whenever possible alongside the analyses.

The randomized groups will be compared at injection visit #1 according to the following variables: adherence to inclusion criteria, epidemiological characteristics, clinical characteristics, and treatments.

The initial comparability of the randomized groups will be evaluated based on key participant characteristics and potential factors associated with the primary outcome measure. Any differences between the groups on these characteristics will be determined based on clinical considerations, not solely statistical ones.

A description of protocol deviations, patients allocated based on these deviations, and reasons for withdrawal will also be provided. The number of enrolled patients and the enrollment curve will be presented by group.

The statistical analyses will first be performed according to the intention-to-treat (ITT) principle, including all patients except those who withdrew consent for the use of their data. A per-protocol analysis will be conducted by excluding patients who were not managed according to their assigned randomization group or who had major protocol deviations.

Comparisons between randomized groups will be conducted systematically (1) without adjustment and (2) with adjustment for factors that may have been imbalanced between the groups despite randomization.

The risk of a type I error will be set at a two-sided 5%. The analyses for secondary objectives will be exploratory in nature, and therefore, no correction for type I error will be applied.

## Primary analysis

The primary objective of this study is to assess the effect of exposure to a music intervention session during the botulinum toxin injection visit #1 on the stress induced by the injection. The primary analysis will rely on a Student's t-test or a Mann-Whitney test, comparing the variation in heart rate variability (HRV) (using the LF/HF ratio) between the randomized groups.

The validity conditions will be verified both graphically and statistically. The equality of variances will be assessed using the Fisher-Snedecor test. The results will be expressed in terms of effect sizes and 95% confidence intervals.

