# STUDY METHODOLOGY

## Evaluation criteria

### Primary endpoint

Patient stress, assessed during Injection Visit #1, will be estimated by changes in Heart Rate Variability (HRV), measured before and during the botulinum toxin injection session using the LF/HF ratio.

The LF/HF ratio is a reliable indicator of the balance between sympathetic and parasympathetic nervous system activity. It provides insight into stress regulation, cardiovascular health, and physiological adaptation. A lower LF/HF ratio may be associated with improved recovery, better emotional regulation, and a healthier autonomic nervous system balance.

HRV will be measured using a Polar H10 heart rate monitor belt. Data will be exported to the Elite HRV application and analyzed using KUBIOS software.

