**V1 (Month 0): Injection visit 1 (inclusion visit)**
At this visit, informed consent will be obtained from the patient or their legal guardian. The physician will provide a copy of the signed consent form to the patient or their legal representative/trustee/designated person. The following data will be collected: age, sex, pathology, and date of first botulinum toxin injection. Once this information is recorded, randomization will be performed by the Clinical Research Associate (CRA) of the department.
For all injections, the same standardized protocol will be applied for each patient (ultrasound-guided or electromyography localization technique, MYOBOT needle [26G], analgesia by ice for palmar or plantar injections upon patient request) in an outpatient setting.

During the first injection visit, a Polar H10 heart rate monitor chest strap will be placed on the patient to measure stress induced by the medical procedure. A minimum recording period of 10 minutes is required prior to the injections to collect reliable baseline data. During this time, the physician will prepare the syringes for botulinum toxin injection. The patient will complete the self-administered anxiety questionnaire (STAI-Y1).

The control group (CT-IM) will not receive any specific intervention other than the Polar H10 heart rate monitor. This group will undergo botulinum toxin injections according to usual practice within the department, with the same evaluations as the intervention group (IM-IM).

The intervention group (IM-IM) will receive a tablet and headphones to listen to music during the botulinum toxin injections. Before the injection, during the waiting time, the patient, with or without assistance, will choose the music to listen to based on personal preferences. The music duration can be adjusted to fit the length of the medical procedure.

At the end of the injection session (both groups), a Visual Analog Scale (VAS) will be presented to the patient to rate pain on a scale from 0 to 10. The nurse or CRA will ask the patient to rate their satisfaction with the intervention using a VAS. Anxiety will be measured using the STAI-Y1 questionnaire. Time perception will also be evaluated based on patient self-report and compared to the actual duration of the medical procedure.

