## Secondary analyses

The main analysis may be supplemented by a multivariate analysis using multiple linear regression to account for covariates selected based on univariate analysis results and their clinical relevance (including sex and age of the patients). Special attention will be given to the study of multicollinearity (Farrar and Glauber test and VIF indicator). The validity of the model (normality of residuals and homogeneity of variances) will be visually assessed. The results will be expressed in terms of regression coefficients, effect sizes, and 95% confidence intervals.

Subgroup analyses will be conducted for the primary endpoint, based on the sex and age of the patients. The interaction between group and subgroup will be explored. The results will be expressed in terms of regression coefficients, effect sizes, and 95% confidence intervals.

Analyses aimed at studying the effect of exposure to a music intervention session during botulinum toxin injections at visit #1, in terms of stress induced by the injection for HRV parameters other than LF/HF, pain induced by the injection, anxiety during the injections, patient satisfaction, and the effect of music intervention on the medical procedure (botulinum toxin injections) as expressed by the physician at the end of the session, will follow the same statistical analysis plan as for the primary endpoint.

Analyses to study the effect of exposure to a music intervention session at visit #2 (to evaluate the effect of repeated exposure to a music intervention) on the variation of stress, pain, variation of anxiety, patient satisfaction, and the effect of music intervention on the medical procedure (botulinum toxin injections) as expressed by the physician at the end of the session, will rely on mixed models.

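### The primary comparison of LF/HF change does not adjust for the pre-injection LF/HF recorded in every patient; it is valid but may give up precision, and the supplementary adjusted analyses leave their covariates largely open

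*Protocol*

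**What the plan says.** The primary endpoint (section 6.1.1) is the change in LF/HF at Injection Visit 1, "measured before and during the botulinum toxin injection session using the LF/HF ratio". Section 7.1 makes the pre-injection value a required measurement: "A minimum recording period of 10 minutes is required prior to the injections to collect reliable baseline data". Section 10.3 then names a t-test or Mann-Whitney test, "comparing the variation in heart rate variability (HRV) (using the LF/HF ratio) between the randomized groups", with no baseline term.

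The sample size is built on the same quantity: "35 patients per group are required to detect an absolute difference in HRV variation, specifically for the LF/HF ratio, of at least 1.8", with an SD of 2.3 (section 10.1).

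Adjustment appears in two other places. Section 10.2 says that group comparisons will be made without adjustment and then "with adjustment for factors that may have been imbalanced between the groups despite randomization". Section 10.4 allows a multiple regression to supplement the main analysis, using "covariates selected based on univariate analysis results and their clinical relevance"; sex and age are the only covariates named. Pre-injection LF/HF is not named as a covariate for the visit 1 comparison. The constrained longitudinal model in section 10.4 adjusts visit 2 for visit 1 values. It does not adjust the visit 1 change for its own starting value. Section 10.4 also carries the primary plan over to the other visit 1 outcomes, including the anxiety change and the other HRV parameters.

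**The concern.** Subtracting the baseline is the same as regressing on it with the slope fixed at 1. The slope that minimises variance is r × SD(during)/SD(before). If that product is not 1, the change score carries avoidable noise. A linear model estimates the slope from the data and in large samples is never less efficient. It also accounts for chance baseline imbalance, which can be appreciable with 40 per arm. The covariate is already collected, so any gain needs no extra patients or measurements.

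The second part is the adjusted result. If covariates are chosen after looking at imbalance or univariate associations, several adjusted estimates are possible, and the protocol does not say which one will be reported beside the primary.

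**Working it through.** **Inputs from section 10.1.** Difference 1.8, SD 2.3 (read as the SD of the change), two-sided 5%, power 90%, 35 per group needed, 40 planned, and effect sizes of 0.5 to 1 usually seen. The low end is 0.5 × 2.3 = 1.15 points.

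**Reproducing the stated size.** n = 2 × [2.3 × (1.960 + 1.282)/1.8]² = 34.3, so 35 per group, as stated. With the noncentral t distribution, power for 1.8 points is 89.7% at 35 and 93.3% at 40. For 1.15 points at 40 it is 59.8%.

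**Effect of baseline adjustment.** Let k = SD(during)/SD(before) and r = the before/during correlation. In units of the variance before injections:

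- Var(change) = 1 + k² − 2rk
- Var(ANCOVA residual) = k²(1 − r²)
- With k = 1 the ratio reduces to (1 + r)/2.
- Residual SD = 2.3 × √ratio, which holds the SD of the change at the protocol's 2.3.

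The protocol gives neither r nor k, so both are assumed. For example, with k = 1.5 and r = 0.5 the ratio is 2.25 × 0.75/(1 + 2.25 − 1.5) = 1.6875/1.75 = 0.96.

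| k | r | Variance ratio | Residual SD | Power at 40, 1.8 points | Power at 40, 1.15 points |
|---|---|---|---|---|---|
| Change score | – | 1 | 2.30 | 93% | 60% |
| 1 | 0.3 | 0.65 | 1.85 | 99% | 78% |
| 1 | 0.5 | 0.75 | 1.99 | 98% | 72% |
| 1 | 0.7 | 0.85 | 2.12 | 96% | 67% |
| 1.5 | 0.3 | 0.87 | 2.15 | 96% | 66% |
| 1.5 | 0.5 | 0.96 | 2.26 | 94% | 61% |
| 1.5 | 0.7 | 1.00 | 2.30 | 93% | 60% |

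Power uses the noncentral t with 78 degrees of freedom for the change score and 77 for ANCOVA.

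**95% CI half-width at 40 per group**, 1.96 × SD × √(2/40): 1.01 for the change score; 0.81/0.87/0.93 for ANCOVA at k = 1.

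**Simulation check** (normal data, r = 0.5, k = 1, 40 per group, 4,000 runs). Both analyses held the type I error at 5.2%. Power at 1.15 points was 60% for the change score and 71% for ANCOVA; at 1.8 points it was 93% and 98%.

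**The case against.** The strongest reply is that nothing here is invalid. The endpoint, the sample size and the test all use the change, the test is unbiased under randomisation, and power at the design difference is adequate. That stands: this is a matter of efficiency. Four stronger readings are tempting, and the documents do not support them.

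- **That change scores always over-correct.** They do so only when r × SD(during)/SD(before) is below 1. At r = 0.5 and an SD ratio of 2 the product is exactly 1, and ANCOVA gains nothing. A larger SD during a stressful procedure is plausible, so the equal-SD figures should not be quoted alone.
- **That the planned rule fails badly if LF/HF is skewed.** Under one assumed log-normal model (log-SD 0.8, r = 0.5, log effect 0.5, 40 per arm), log-scale ANCOVA reaches 89% power. The planned rule gives 62% to 78%, depending on how the choice between tests is read. Raw-scale ANCOVA gives only about 75%, so that gain comes largely from the log scale, in a model that favours it. The protocol gives no distribution for LF/HF.
- **That the open covariate choice undermines the primary result.** Section 10.3 designates the unadjusted comparison. The section 10.4 regression is optional and supplementary, names sex and age, and asks for clinical relevance. Section 10.2 likewise says that imbalance is not judged on statistics alone. A simulated false-positive rate of 8.0% came from taking the best of three analyses, one of which is not planned, so it does not describe this trial.
- **That ANCOVA is automatically sound here.** Section 7.1 places randomisation before the chest strap and baseline recording, and section 8.2 has headphones worn before the procedure. The covariate is sound only if allocation cannot affect the baseline window. The change score needs the same condition, so this does not favour the present plan.

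A full covariate list may also be left to a SAP. That is fair, but the protocol itself already fixes the unadjusted primary test and the two selection rules.

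**Conclusion.** The point holds as one of precision and of an open supplementary analysis. It is not a finding of bias, an inflated primary error rate or a wrong sample size.

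For r between 0.3 and 0.7, the variance saving is 15% to 35% with equal SDs, and about 0% to 13% if the SD during injections is 1.5 times the SD before. At the design difference the trial is well powered either way. The gain matters most if the true effect is near 0.5 SD, where the planned test has 60% power at 40 per group. All of this rests on reading 2.3 as the SD of the change, on assumed values of r and of the SD ratio, and on a baseline window unaffected by allocation.

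**What to change.** - Make the primary analysis one pre-specified linear model of during-injection LF/HF on group and pre-injection LF/HF. Fix the scale, raw or log, in advance.
- Name any further covariates, such as age and sex, in advance. Drop selection by observed imbalance and by univariate results.
- Use the same form for the visit 1 STAI change and the other visit 1 HRV changes.
- Keep the unadjusted comparison of change as a sensitivity analysis.
- State in sections 7.1 and 8.2 that the baseline window at visit 1 is music-free in both arms, and preferably recorded before allocation is revealed.

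The cost is mostly wording in the protocol and SAP, with no extra patients or measurements. There are two small downsides. A log-scale result is a ratio, so the raw difference should be reported alongside for comparison with the 1.8 points. Recording baseline before allocation would change the order of steps at visit 1.

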## Secondary analyses

The main analysis may be supplemented by a multivariate analysis using multiple linear regression to account for covariates selected based on univariate analysis results and their clinical relevance (including sex and age of the patients). Special attention will be given to the study of multicollinearity (Farrar and Glauber test and VIF indicator). The validity of the model (normality of residuals and homogeneity of variances) will be visually assessed. The results will be expressed in terms of regression coefficients, effect sizes, and 95% confidence intervals.

Subgroup analyses will be conducted for the primary endpoint, based on the sex and age of the patients. The interaction between group and subgroup will be explored. The results will be expressed in terms of regression coefficients, effect sizes, and 95% confidence intervals.

Analyses aimed at studying the effect of exposure to a music intervention session during botulinum toxin injections at visit #1, in terms of stress induced by the injection for HRV parameters other than LF/HF, pain induced by the injection, anxiety during the injections, patient satisfaction, and the effect of music intervention on the medical procedure (botulinum toxin injections) as expressed by the physician at the end of the session, will follow the same statistical analysis plan as for the primary endpoint.

Analyses to study the effect of exposure to a music intervention session at visit #2 (to evaluate the effect of repeated exposure to a music intervention) on the variation of stress, pain, variation of anxiety, patient satisfaction, and the effect of music intervention on the medical procedure (botulinum toxin injections) as expressed by the physician at the end of the session, will rely on mixed models.

Specifically, the study of longitudinal repeated data will be performed using random-effects models, which allow for the study of fixed effects (groups, evaluation time, and their interaction) while accounting for inter- and intra-patient variability. To compare between randomized groups, the means of the quantitative criteria evaluated at visits #1 and #2 will be analyzed using a mixed linear model of constrained Longitudinal Data Analysis (cLDA). In this model, the dependent variable includes both values at visit #1 and post-inclusion values, and the mean difference at visit #1 between groups is constrained to 0. This model allows the calculation of changes between visit #1 and each follow-up time point (here, visit #2), while adjusting for values at visit #1. The difference between groups is obtained through the interaction between time and the randomization group. The model will include different random effects at the patient level (a model with random intercepts and slopes, allowing for variation between patients in both baseline values and changes in the outcome over time). The model parameters will be estimated using the restricted maximum likelihood (REML) method. Intra-group randomization analyses will also be performed.

For categorical criteria, a generalized linear mixed model with logit link of the type cLDA (constrained Longitudinal Data Analysis) will be considered. In this model, the dependent variable includes both inclusion and post-inclusion values, and the event difference between the two groups is constrained to 0. This model allows for the calculation of odds ratios at each follow-up time point (visit #2), adjusting for values at visit #1. The subject effect will be treated similarly to what was previously described.

Comparisons between randomized groups not involving repeated data will use conventional statistical tests: (1) Student's t-test or Mann-Whitney test if t-test assumptions are not met (normality and homoscedasticity assessed using the Fisher-Snedecor test) (e.g., for patient satisfaction) and (2) Chi-squared test or, if applicable, Fisher's exact test.

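### The visit 2 mixed model (cLDA) fixes the visit 1 group difference at 0, but only one arm has music at visit 1, so the secondary repeated-exposure contrast is biased by part of any visit 1 music effect

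*Protocol*

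**What the plan says.** Section 10.4 (Secondary analyses) assigns the visit 2 outcomes to mixed models: variation of stress, pain, variation of anxiety, satisfaction and the physician's rating. For quantitative criteria it specifies a constrained longitudinal data analysis (cLDA) of the visit 1 and visit 2 values, in which "the mean difference at visit #1 between groups is constrained to 0". The effect is then read off as follows: "The difference between groups is obtained through the interaction between time and the randomization group". For categorical criteria a logit version is proposed in which, likewise, "the event difference between the two groups is constrained to 0".

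Section 7.1 describes visit 1. Randomisation takes place there, before the recording and the injections. IM-IM then has music, whereas for the other arm: "The control group (CT-IM) will not receive any specific intervention other than the Polar H10 heart rate monitor". At visit 2 both arms have music.

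Section 10.1 bases the sample size on a visit 1 group difference in LF/HF variation "of at least 1.8 with a standard deviation of 2.3". Section 10.3 tests that same visit 1 difference as the primary analysis.

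**The concern.** A cLDA constraint is justified when the first time point precedes any difference in treatment, because randomisation then makes the arm means equal in expectation. Visit 1 is not such a time point. The modelled outcomes are measured during or after the visit 1 injections, with music in one arm and none in the other. Pain, satisfaction and the physician's rating have no pre-injection value at all. The protocol thus expects and tests a non-zero difference at visit 1 and then fixes the same quantity at 0.

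The group comparison at visit 2 (second exposure in IM-IM, first exposure in CT-IM) is at stake. The forced equality pushes part of the visit 1 music effect into that comparison with the sign reversed. The better music works at visit 1, the more a second exposure appears inferior to a first.

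**Working it through.** **1. The plan's own figure.** Inputs from section 10.1: difference 1.8, SD 2.3, two-sided 5%, power 90%. Normal approximation: n = 2 × (1.960 + 1.282)² × (2.3/1.8)² = 2 × 10.51 × 1.633 = 34.3, so 35 per group. This agrees with "35 patients per group are required to detect an absolute difference in HRV variation". The exact t-test gives 36, a trivial difference. The planned 40 per group gives about 93% power. The sample size is sound and is not in dispute.

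**2. What the constrained model estimates.** Let D1 and D2 be the true group differences (IM-IM minus CT-IM) at visits 1 and 2, and r the within-group slope of visit 2 on visit 1, which equals the correlation if the SDs are equal. With visit 1 means forced equal, the visit 2 contrast is

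estimate = D2 − r × D1.

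**3. Numbers.** D1 = −1.8 (music lowers LF/HF by the design effect), SD 2.3, 40 per arm. Both arms have the same benefit at visit 2, so D2 = 0. The protocol gives no between-visit correlation, so r from 0.2 to 0.7 is an assumption. The last two columns are from 500 simulated trials per row, fitted by REML with unstructured covariance.

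| r | −r × D1 | mean simulated estimate | rejections at nominal 5% |
|---|---|---|---|
| 0.2 | +0.36 | +0.38 | 15% |
| 0.3 | +0.54 | +0.53 | 23% |
| 0.5 | +0.90 | +0.89 | 54% |
| 0.7 | +1.26 | +1.29 | 93% |

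Hand check at r = 0.5: the model's standard error is about 2.3 × √(1 − 0.25) × √(2/40) = 0.445, and 0.90/0.445 = 2.02. That is close to the 1.96 threshold, so rejection in roughly half of trials is expected. Compound symmetry gives estimates of +0.45 to +1.29 over the same range of r.

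**4. Is the constraint the cause?** With D1 = 0 the contrast is about 0 and rejection is 4% to 7%. With D1 = −1.8 and visit 1 means left free, the mean visit 2 contrast is −0.05 to +0.06, against a true 0.

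**5. Within-arm changes from the same model.** The forced common visit 1 mean lies midway between the arms, 0.9 from each. The modelled change is therefore −0.9 − 0.9r in CT-IM (true −1.8) and −0.9 + 0.9r in IM-IM (true 0). At r = 0.5 these are −1.35 and −0.45. The simulated CT-IM change ran from −1.10 to −1.54 over r = 0.2 to 0.7.

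**6. Reading the interaction as a difference in change.** Its true value is D2 − D1 = +1.8, and the constrained model gives about +0.9 at r = 0.5. Without the constraint the interaction does estimate +1.8, but that is the disappearance of the visit 1 contrast once both arms have music. It is not an effect of repeated exposure.

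**The case against.** The strongest reply concerns scope. Section 6.3 makes the visit 2 comparison a secondary objective, and section 10.2 calls the secondary analyses exploratory, without type I error correction. The primary test, the sample size and the visit 1 secondary tests do not use this model. All of that stands, and it limits the severity. It does not excuse the constraint: exploratory status covers the lack of multiplicity control, not a bias of known direction.

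The size is also conditional. It takes the full 1.8, which section 10.1 draws from a virtual-reality study, and an assumed r. A reader might infer that false-positive rates of 54% or 93% are to be expected in this trial. The documents do not support that, since neither the true music effect nor r is known. The rates also depend on the test. Regressing visit 2 on visit 1 and group gives essentially the same point estimate but rejects in about 17%, 45% and 88% of trials at r = 0.3, 0.5 and 0.7. The rates in the table are those of the planned type of model.

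A reader might also suppose that a proper baseline is at hand and that the constraint need only be moved to it. In section 7.1, however, the heart rate recording and the STAI-Y1 follow randomisation. Section 8.2 has the headphones worn before the procedure as well as during it, and section 7.1 does not say when music starts at visit 1. As written, no value precedes allocation, and the pre-injection recording in IM-IM may be made under music.

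Satisfaction cannot simply be counted among the affected outcomes. Section 10.4 lists it under mixed models and later gives it as an example of a non-repeated comparison by t-test or Mann-Whitney.

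Finally, the protocol does not define repeated exposure solely as the visit 2 group difference, since it also plans within-arm analyses. Those may be reported, but they are not randomised comparisons, and the constraint distorts them too if they are taken from this model.

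**Conclusion.** The model is wrong as written for this design. Its visit 2 contrast carries a bias of −r × D1. At the design effect of 1.8, with no true repeated-exposure effect, that is about +0.54, +0.90 or +1.26 LF/HF units for assumed r of 0.3, 0.5 or 0.7, or 30%, 50% or 70% of the design effect. Because a lower LF/HF ratio is taken as favourable, repeated exposure would look worse than first exposure. If music has no visit 1 effect there is no bias. The logit version has the same flaw, but its size was not calculated.

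A reader might infer that the trial's main conclusion is at risk. It is not: the primary analysis is a direct comparison at visit 1. The point should be fixed before analysis, and it does not threaten the primary result.

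**What to change.** Reword section 10.4:

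- Remove the visit 1 constraint from both the linear and the logit model, and leave group means free at both visits.
- Report two separate contrasts: the visit 1 group difference (music versus none) and the visit 2 group difference (second versus first exposure). Do not present the time-by-group interaction as the repeated-exposure effect.
- Adjust HRV or STAI-Y1 for the visit 1 pre-injection value only if that value is taken before music starts. Otherwise use no baseline constraint. Pain, satisfaction and the physician's rating have no such value.
- State once whether satisfaction is analysed by mixed model or by t-test/Mann-Whitney.
- Label within-arm changes as non-randomised comparisons.

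The cost is a rewording, with no new patients or data. A baseline taken before allocation would require a change to the order of visit 1, but the fix does not depend on one.

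### Section 10.4 fixes random intercepts and slopes for outcomes with only two values per patient: over-parameterised if the effects are correlated, wrongly constrained if they are independent

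*Protocol*

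**What the plan says.** Section 10.4 assigns the visit 2 analyses to mixed models and lists their outcomes: "on the variation of stress, pain, variation of anxiety, patient satisfaction, and the effect of music intervention on the medical procedure". For quantitative criteria, "the means of the quantitative criteria evaluated at visits #1 and #2 will be analyzed using a mixed linear model" of the constrained longitudinal type, with visit 2 as the only follow-up point. On the covariance side it states that "The model will include different random effects at the patient level", and explains this as "a model with random intercepts and slopes, allowing for variation between patients in both baseline values and changes in the outcome over time". Estimation is also fixed: "The model parameters will be estimated using the restricted maximum likelihood (REML) method". For categorical criteria it adds: "The subject effect will be treated similarly to what was previously described".

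The section does not say whether intercept and slope are correlated, how visits are coded, or whether the residual variance is constrained.

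**The concern.** A random slope needs enough occasions per patient to be told apart from residual error, and two occasions are not enough. Stress and anxiety enter as one change per visit. Pain and the physician's rating are single scores per visit, as is satisfaction if it is analysed by mixed model. Each patient therefore contributes at most two observations to any one model.

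Two things are at stake. If the software cannot fit the stated model, the analyst has to pick a simpler one after seeing the data. If the random effects are made independent so that the model runs, it carries a hidden assumption that variability does not fall from visit 1 to visit 2. At visit 1 one group has music and the other does not; at visit 2 both have it. A smaller spread at visit 2 is therefore plausible, though not established.

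**Working it through.** **Inputs.** Two visits, random intercept and slope, REML (section 10.4). SD 2.3 for the change in LF/HF ratio and 40 patients per group (section 10.1). That SD belongs to the protocol's own sample size, which reproduces: 2 × (2.3 × (1.96 + 1.2816) / 1.8)² = 34.3, so 35 per group. The protocol gives no visit 2 SD and no between-visit correlation. I assume a correlation of 0.5 and visit 2 SDs of 1.6, 1.2 and 3.0.

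**Correlated effects.** Let a be the intercept variance, b the slope variance, c their covariance and s the residual variance. With visits coded 0/1:

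- Var(visit 1) = a + s
- Cov = a + c
- Var(visit 2) = a + b + 2c + s

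That is four unknowns in three equations. Replacing (s, a, c, b) by (s + t, a − t, c + t, b − 2t) leaves all three unchanged. For variances 4.5 and 5.1 with covariance 2.8:

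| s | a | c | b |
|---|---|---|---|
| 0.5 | 4.0 | −1.2 | 3.0 |
| 1.0 | 3.5 | −0.7 | 2.0 |
| 1.5 | 3.0 | −0.2 | 1.0 |

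All three rows are admissible and give the same likelihood. The line ends before s = 2.0, where b = 0 with c = 0.3 is not a valid covariance matrix (smallest eigenvalue −0.035). The rank of the mapping from parameters to moments is 3 of 4 for codings 0/1, 1/2 and −0.5/+0.5. With three visits it is 4 of 4.

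**Independent effects (c = 0).**

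- Coded 0/1: Var(visit 2) − Var(visit 1) = b ≥ 0, and Cov = a ≥ 0. The model is just identified but constrained. Coding 1/2 imposes the same ordering.
- Coded −0.5/+0.5: the variances are forced to be equal and the rank is 2 of 3, so it is again not identified.

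**Size when spread falls.** The slope variance is then estimated at or near its boundary of zero. Both visits get the average variance p = (SD₁² + SD₂²)/2, and the covariance k is kept. With the section 10.4 constraint of equal visit 1 means, the visit 2 value is adjusted with slope β = k/p. Then

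- reported SE = √[(2/40)(p − k²/p)]
- true SE = √[(2/40)(SD₂² − 2βk + β²SD₁²)]

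Visit 2 SD 1.6: p = (5.29 + 2.56)/2 = 3.925, k = 0.5 × 2.3 × 1.6 = 1.84, β = 0.469. Reported SE = √(0.05 × 3.062) = 0.391. True SE = √(0.05 × 1.997) = 0.316.

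Visit 2 SD 1.2: p = (5.29 + 1.44)/2 = 3.365, k = 1.38, β = 0.410. Reported SE = √(0.05 × 2.799) = 0.374. True SE = √(0.05 × 1.198) = 0.245.

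**Simulation.** 400 trials per row, no group effect, correlation 0.5, visit 1 SD 2.3. Each cell gives mean model SE / empirical SE / type I error at nominal 0.05.

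| Visit 2 SD | Independent intercept and slope | Unstructured 2x2 |
|---|---|---|
| 1.6 | 0.390 / 0.328 / 0.025 | 0.307 / 0.326 / 0.070 |
| 1.2 | 0.372 / 0.243 / 0.008 | 0.230 / 0.228 / 0.055 |
| 2.3 | 0.449 / 0.424 / 0.048 | 0.440 / 0.421 / 0.052 |
| 3.0 | 0.572 / 0.584 / 0.060 | 0.572 / 0.584 / 0.060 |

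The Monte Carlo error of a 5% rate over 400 trials is √(0.05 × 0.95/400) = 0.011, so 0.070 lies within two such errors of nominal. With equal SDs and a correlation of −0.2, the independent model sets the covariance to 0 (unstructured: −1.07), with little effect on type I error.

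**The case against.** The best defence is that the protocol names intercepts and slopes only. Their covariance and the time coding are details that a statistical analysis plan normally settles, and with independent effects coded 0/1 the model is identified. This stands as far as it goes, but it does not clear the text. The protocol itself commits to a random slope on two occasions, and each way of completing that specification examined here is either unidentified or imposes a constraint on the variances that nobody has argued for.

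The extra raw readings do not help either. HRV is measured before and during the session and the STAI-Y1 before and after it, but section 10.4 models their change, which is one value per visit.

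Some stronger readings are tempting and should be resisted:

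- *The visit 2 effect cannot be estimated.* It can. With correlated effects the likelihood depends only on the 2x2 marginal covariance, which is identified. The group-by-time effect and its SE are the same for every equivalent parameter set. Convergence failure is possible, not certain.
- *The model produces false positives.* When spread falls the SE error is conservative. When spread rises the two models agree.
- *Every visit 2 quantitative endpoint is affected.* Section 10.4 lists satisfaction under mixed models, but later gives it as an example for a t-test or Mann-Whitney test, so its place is unclear.
- *The trial's main result is at risk.* The primary analysis is a two-group test at visit 1 (section 10.3), and section 10.2 calls the secondary analyses exploratory.

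**Conclusion.** The random-effects specification in section 10.4 is wrong for two visits and should be changed. With correlated effects it has one parameter too many: variance components are arbitrary and the fit may fail, but the reported treatment contrast survives. With independent effects coded 0/1 or 1/2 it rules out a fall in variance and a negative covariance. If variance does fall, the SE of the group-by-time effect is too large by about 24% (0.391/0.316) for a visit 2 SD of 1.6 and about 53% (0.374/0.245) for 1.2, and power is lost.

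Those sizes rest on SD 2.3 from section 10.1 and on an assumed correlation and assumed visit 2 SDs. The documents do not show that spread will fall, and if it rises there is no cost. The damage is confined to exploratory secondary analyses. The effect of carrying the same random effects into the logit model was not calculated.

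**What to change.** In section 10.4, replace the random intercept and slope for quantitative criteria by an unstructured 2x2 within-patient covariance (two variances and one covariance, no random effects), fitted by REML. This has three parameters for three moments and imposes no ordering of the variances. For the logit model, specify a random intercept only, in place of the carry-over of the same subject effects.

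The repair leaves the mean structure as it stands. Whether visit 1 means should be constrained to be equal is a separate question that this change neither settles nor depends on. The cost is one sentence for the linear model and a few words for the logit model, with no change to data collection or sample size. Making it before the data are seen removes the need for a data-driven simplification later.
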